**Data analysis:**

We will document the proportion of participants who consent and get recruited, the proportion of those who will get retained and reasons for drop out. We will conduct an intention to treat analysis comparing the groups at weeks 4, 12, 24 and assess the effect of the intervention on the clinical outcomes (described above). We will use the Bonferroni approach to correct for multiple comparisons.

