#### Blinding participants and RA to the study arm

Participants will be randomly assigned to the study arms. The RA and participants will all be blinded to the study arm they will be allocated before consent. VHTs will deliver 6 psycho-education sessions (1 per month) to participants in intervention arm and their family members at the participant’s residence. The PI and RAs will sit in some of the sessions during the first 2–3 sessions of data collection to ensure fidelity to the manual. We will conduct 5 exit focus group discussions with patients and family members to assess acceptability to the use of the manual. Participants in the control arm will get usual treatment. RA’s will schedule participants from both arms for an assessment using the same instruments at weeks 4, 12 and 24 at the clinic. We will have a separate set of RA’s for the intervention arm and another for the control arm to ensure blinding of the RA.

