### The intervention

After discharge, the program manager will link the participants with a VHT nearest to them. The participants (randomized to the intervention arm) will be informed during the consent procedure that they will undergo 6 psycho-education sessions (1 per month) together with a family member at the participant’s residence. The VHTs and participants will meet and schedule appointments for the next engagements. This shall be done on a case by case basis. Some psycho-education sessions could take place in the patient’s residence, others in the nearest public space (school or church or mosque compounds). We will document where the majority of these sessions happen. This will help us document feasibility. The PI and RAs will sit in some of the sessions during the pilot phase of data collection to ensure fidelity to the manual.

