### Data analysis plans

We will report the duration of recruiting participants and the proportion of eligible patients who get recruited. We will compare the demographic parameters (age, gender, education status) as well as disease severity. We will compare the proportion of participants who are retained in the study at week 4, 12 and 24 as well as mean differences in adherence, stigma, illness management ability and symptom severity (PANSS or YMRS) scores between the intervention and control arms. We will use the Bonferroni approach to correct for multiple comparisons.

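### Bonferroni is fixed for comparisons at weeks 4, 12 and 24 without a defined family; Holm on the week-24 clinical outcomes would keep the same error control and lose less power

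*Protocol article*

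**What the plan says.** The section Data analysis plans lists retention by visit ("We will compare the proportion of participants who are retained in the study at week 4, 12 and 24") and then "mean differences in adherence, stigma, illness management ability and symptom severity (PANSS or YMRS) scores between the intervention and control arms". It closes with "We will use the Bonferroni approach to correct for multiple comparisons". In that section the visit list is attached to retention, and the clinical outcomes follow it. The abstract is more direct and applies the visits to the clinical outcomes: "We will conduct an intention to treat analysis comparing the groups at weeks 4, 12, 24 and assess the effect of the intervention". It, too, names Bonferroni. Neither place gives an alpha, a number of tests or a main visit for efficacy.

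On exposure, the section on blinding states "VHTs will deliver 6 psycho-education sessions (1 per month) to participants in intervention arm". The section The intervention gives no fixed day for the first session: "After discharge, the program manager will link the participants with a VHT nearest to them". The blinding section sets assessments at weeks 4, 12 and 24. The section Follow-up sets them at month 3 and six-monthly after that.

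**The concern.** A Bonferroni correction divides alpha equally over every test in the family. If the family spans all three visits, the week-24 comparison, which lies closest to full exposure, gets no more of the error budget than a week-4 comparison made after about one session. The early visits cannot assess the six-session programme, yet testing them formally raises the threshold at the visit that comes nearest to doing so. Holm's step-down procedure controls the same family-wise error rate and is never less powerful. At stake is the chance that this small pilot declares an effect at week 24.

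**Working it through.** **Inputs from the protocol article.** Four clinical outcomes (Data analysis plans); three visits (abstract); 40 per arm (abstract, Methods); 80% retained at 24 weeks (Hypothesis), so 0.80 × 40 = 32 per arm; six sessions, one per month.

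**Assumptions, because the article gives no figures.** Overall two-sided alpha 0.05; equal arms; standardised effect 0.5, with 0.7 as a second case; correlation 0.4 between outcomes.

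**The plan's own figure.** Sample size estimation says that 80 participants allow a 5% difference in mean scores to be detected. It gives no SD, so this cannot be reproduced.

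**Share of alpha.** 4 × 3 = 12 tests; 0.05/12 = 0.00417 each. Week 4 takes 4 × 0.00417 = 0.0167, one third of alpha. Week 12 takes the same, so the two early visits take two thirds. The share stays at one third per visit with 15 tests (retention added, or PANSS and YMRS tested separately: 5/15), or with correction over visits within each outcome. It does not apply if the correction runs over the four outcomes separately at each visit; week 24 is then already tested at 0.05/4 = 0.0125.

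**Exposure.** With a month of 4.35 weeks:
- A first session on day 0 puts the second at week 4.35 and the sixth at 5 × 4.35 = week 21.8.
- A first session one month after discharge puts the sixth at 6 × 4.35 = week 26.1.
- The sixth session falls by week 24 only if the first is by about 24 − 21.75 = week 2.25.
- With four-week spacing the sixth falls at weeks 20 to 24, and a second session could fall at week 4.

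**Power per outcome at 32 per arm (normal approximation).** Power ≈ Φ(d·√(n/2) − z(1−α/2)). For d = 0.5, d·√(32/2) = 2.0.
- Bonferroni over 12: Φ(2.0 − 2.865) = Φ(−0.865) = 19.3%.
- Bonferroni over 4: Φ(2.0 − 2.498) = Φ(−0.498) = 30.9%.
- Bonferroni over 5 (PANSS and YMRS separate): Φ(2.0 − 2.576) = Φ(−0.576) = 28.2%. The PANSS and YMRS tests would have fewer than 32 per arm and so less power than this.

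Holm over four tests was simulated (200,000 runs, correlation 0.4):

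| True effects | Bonferroni over 12 | Bonferroni over 4 | Holm over 4 |
|---|---|---|---|
| 0.5 SD, one of four | 19% | 31% | 31% |
| 0.5 SD, two of four | 19% | 31% | 32% |
| 0.5 SD, all four | 19% | 31% | 37% |
| 0.7 SD, all four | 47% | 62% | 71% |

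At 0.5 SD, the smaller family adds 30.9 − 19.3 = 11.6 points. Holm adds a further 0 to 6.

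**Detectable difference, 80% power, 32 per arm.** By (z(1−α/2) + 0.842)·√(2/32): 0.93 SD at 0.05/12 and 0.84 SD at 0.05/4. With the noncentral t these are 0.96 and 0.86 SD.

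**The case against.** The strongest reply is that the 12-test family is nowhere stated. A reader might infer that the plan does test week 24 at one twelfth of alpha. The article does not support this as fact: it names the method and the visits, not the family, and a within-visit correction would remove the loss. That stands. The exact family may be left to an analysis plan that is not shown, so its absence is not counted here as an omission. What remains is the method and the visits that the article does fix.

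A reader might also infer that Bonferroni is an error. It is not; it controls family-wise error, and Holm is an improvement on it. Nor is Holm the main source of gain: its 37% needs all four effects to be real, and it adds nothing to the chance of at least one rejection.

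The claim that no more than one session can precede week 4 holds for spacing by calendar month and may fail with four-week spacing, so "about one" is as far as the text goes.

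Some would want a formal test at week 12, about halfway through the programme. That is a legitimate preference. So are visit-by-visit means, which the article does not require to be replaced by a repeated-measures model.

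Finally, efficacy is secondary and preliminary, no formal power calculation is claimed, and the effect size to be carried into a powered trial does not depend on the multiplicity threshold. All of this limits the consequence but does not make testing the early visits under Bonferroni the better choice.

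**Conclusion.** The point holds as a low-cost improvement to a valid but conservative choice. On the natural reading, two thirds of alpha is spent at visits that precede most of the intervention. Confining the tested family to week 24 raises power per outcome from about 19% to 31% at 0.5 SD, and Holm takes it to between 31% and 37%. These figures rest on the assumed alpha, effect sizes, correlation and equal arms of 32, and on severity being one outcome. They cannot be tied to the 5% difference in the article.

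It would be too strong to conclude that the change gives the pilot adequate power: even the best case at 0.5 SD is 37%. Week 24 is the visit nearest full exposure, but the article's calendars do not ensure that all six sessions come before it.

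**What to change.** In Data analysis plans, and in the matching sentence of the abstract:
- Define the tested family as the clinical outcomes at week 24, with the overall two-sided alpha stated.
- Count PANSS and YMRS as two tests if they are analysed separately.
- Replace Bonferroni with Holm.
- Report weeks 4 and 12 as between-arm estimates with 95% confidence intervals.
- Report the number of sessions each intervention participant received before the week-24 assessment.

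Before the family is fixed, three statements must be reconciled: the monthly session calendar (blinding section and The intervention), the assessments at weeks 4, 12 and 24 (blinding section), and the month-3 and six-monthly schedule (Follow-up). Otherwise neither the week-24 visit nor the exposure at it is certain.

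The analysis change costs wording only and needs no further participants. Its price is that no formal significance claim can be made at weeks 4 and 12.

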### Ethics and dissemination plans

This work received ethical permission from the Makerere University School of Medicine Research and Ethics Committee IRB approval number (**Rec Ref 2020–161**). Uganda National Council for Science and Technology (**HS 1026ES**).

#### Ethical considerations

We will have a two-layered consent process. (i) Trained RAs will read the consent form to the participant, then (ii) administer the UBACC to ensure that participants have fully understood the rationale for conducting the study and that they are participating well aware of their rights as participants.

A few ethical considerations are worth pointing out—beyond the distress that participants may experience, this will be a minimal risk study. To minimize the risk of loss of confidentiality and privacy, only the investigators will have access to the study records and test results and the link between personal identifying information and study data. No individual identities will be used in any reports or publications associated with the data from this study. All softcopies of the data will be stored in password locked computers. Hard copies of the questionnaires will be stored in locked file cabinets at the study offices in Butabika National Referral Hospital.

#### Dissemination plans

A manuscript will be prepared from these findings and submitted to peer reviewed journal for publication. Findings will also be presented at local and international conferences. We will hold a dissemination workshop and provide results to the patients who have participated in the pilot phase as well as other stakeholders to whom these findings are important in shaping policy and practice.
